### Outcome measures

2.10

#### Primary outcome

2.10.1

The primary outcome is the reduction of specific DMUD (GD, PSMU, or VSD) symptoms assessed by the DMUD test battery for adolescents and parents based on differential scores in pre–post comparison.

It includes the Gaming Disorder Scale for Adolescents/Parents (GADIS-A/-P), the Social Media Disorder Scale for Adolescents/Parents (SOMEDIS-A/-P), and the Streaming Disorder Scale for Adolescents/Parents (STREDIS-A/-P). All 10-item scales are identical except for the initial explanation and continuous naming of the specific digital medium of interest (digital games, social media platforms, and video-streaming services) and address either the potentially affected adolescent (self-rating version) or the respective parent (external-rating version). The whole test battery is based on the ICD-11 criteria of GD and has been adapted for SMUD and VSD accordingly. It has been validated in large nationally representative adolescent–parent samples and showed profound psychometrical properties with good to excellent internal consistency, criterion validity, and discriminatory power (12, 15, 40, 55, 65, 66). Accordance between self-rating and parental rating was moderate. Moreover, GADIS-A has been evaluated with Persian and Russian adolescents with good to very good internal consistency and adequate to very good retest reliability (67, 68). Adolescents and parents indicate their agreement with nine statements on a five-point Likert scale (strongly disagree [0]–strongly agree [4]) under consideration of the past 12 months with higher total scale scores resembling more problems. The 10th item reflects the frequency of problems, conflicts, or difficulties due to the digital medium and is answered by choosing one out of four response options (not at all [0]–nearly daily [3]). The questionnaires can be used for a categorical assessment of the DMUD. Accordingly, a score of ≥2 is considered significant regarding the ICD-11 criteria. Moreover, factor analyses confirmed two underlying scale factors, one for *cognitive-behavioral symptoms* (CBS) of problematic media usage and one for *negative consequences* (NC) of the media usage pattern. Cutoffs between scales are comparable, although slightly differing. For GADIS-A and GADIS-P, these are >9 (CBS) and > 5 (NC), for SOMEDIS-A and SOMEDIS-*p* > 8 (CBS) and > 6 (NC), and for STREDIS-A and SOMEDIS-*p* > 6 (CBS) and > 11 (NC).

Children and adolescents will be classified as disordered if the cutoffs for both factors are reached and the time criterion is met. Reaching the cutoff of CBS only suggests hazardous media use. In the clinical context, the DMUD test battery has been regularly used and could prove to be helpful in assessing potential symptom changes during therapy.

Additionally, each treating clinician will assess symptom expression, rate fulfillment of the ICD-11 criteria (based on criteria of GD), and diagnosis of a potential specific DMUD. They will be provided with a digital criterion checklist including examples to enhance interpretation based on ICD-11 suggestions, the clinical interview guideline of the Gaming Disorder and Hazardous Gaming Scale (GDHGS) (69), and clinical expert experience.

In the case of the diagnosis of more than one DMUD, the clinically most prominent one (i.e., by total rating scores and clinical evaluation) will be defined as the main DMUD. This will be addressed during intervention and used as a primary outcome, which was assessed during enrollment, at post-intervention, and follow-up. The differences between screening and post-intervention total scale scores will be investigated primarily.

#### Secondary outcomes

2.10.2

Secondary outcomes can be divided into psychological, media-associated, parental, and family-associated factors and are assessed with the participating adolescents and parents separately (Table 1). For adolescents, these include adolescent emotional and behavioral problems (based on self-rating and parental rating), sleep-associated aspects, mindfulness, and psychological stress perception, media usage times, and family communication/functioning. For the parents, these comprise mindfulness, quality of life, parental media usage, media rules, parental self-efficacy, and family communication/functioning.

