**Methods:**

Res@t digital (Resource-Strengthening Training for Adolescents with Problematic Digital-Media Use and their Parents) is the app-based translation of the first model-based digital intervention for adolescents with DMUD and their parents based on CBT. It comprises separate but content-related modules for adolescents (Res@t–A) and parents (Res@t–P), applying multimodal techniques. The effectiveness of Res@t will be evaluated within a multicenter cluster-randomized controlled evaluator-blinded pre–post follow-up trial with the waitlist control group (CG). In addition to the Res@t program in the intervention group, both groups will receive treatment as usual within primary child and adolescent psychiatric/psychotherapeutic healthcare. The primary outcome addresses DMUD symptom reduction after 10 weeks. Secondary outcomes are related to a reduction in psychological and family-related problems and an increase in parental self-efficacy. All outcomes will be assessed using standardized self-report measures. A total of 1,334 participating adolescent–parent dyads from a large clinical network throughout Germany are planned to be included in the primary analyses based on an intention-to-treat approach, applying linear mixed models.

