### Aim of the study and hypotheses

1.1

The present study aims to evaluate the effectiveness of a new model-based standardized online intervention program, the Resource-Strengthening Training for Adolescents with Problematic Digital-Media Use, and their Parents (Res@t digital) in an outpatient setting. The Res@t digital intervention group (IG) will be compared with a waiting control group (CG). The IG will receive the Res@t digital intervention, and both groups will receive treatment as usual (TAU) during the study period. The waitlist CG will be offered access to the intervention after individual data collections are completed. It is hypothesized that Res@t digital + TAU is superior to TAU only and will lead to a decrease in adolescent DMUD (i.e., GD, SMUD, or VSD) symptoms. In the case of an adolescent being affected by more than one DMUD or hazardous use pattern, the clinician will identify the most prominent phenomenon that will be focused on within the targeted intervention. Moreover, Res@t digital will reduce mental-health-related problems in adolescents and increase parental self-efficacy.

There are three primary hypotheses structured hierarchically which address the one most prominent DMUD or hazardous use pattern in the individual adolescent identified by the clinician (i.e., PG, PSMU, or PVS). This is referred to the term “specific” DMUD:

First primary hypothesis: Res@t + TAU reduces symptoms of specific DMUD in adolescents compared with TAU, measured as change from screening to post-intervention. Second primary hypothesis: Res@t + TAU reduces symptoms of specific DMUD in adolescents assessed by their parents compared with TAU, measured as change from screening to post-intervention. Third primary hypothesis: Res@t + TAU reduces symptoms of specific DMUD in adolescents assessed by their treating clinicians compared with TAU, measured as change from screening to post-intervention.

To the best of our knowledge, although positive effects of online interventions have been repeatedly suggested to fill substantial treatment gaps for mental health issues in adults (27–29) and adolescents (30–32) including addictive behavior (33–35), no comparable intervention for adolescents with DMUD and their parents is available yet. Therefore, Res@t strives to close a significant void.

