	Family Communication Scale (FCS)	Family communication	10 Items	(51, 56)
	Patient Health Questionnaire-9 (PHQ-9)	Parental depression	9 Items	(57–59)
	Generalized Anxiety Disorder-7 (GAD-7)	General anxiety of parents	7 Items	(58, 60)
	Parenting Inventory – Revised (EEI-R)	Parenting style (without subscale about religion)	44 Items	(61)
	Questionnaire on Self-Efficacy in Parenting (FSW)	Parental self-efficacy	9 Items	(62)
	Perceived Stress Scale (PSS-10)	Psychological stress perception	10 Items	(47, 48)
	Ulm Quality of Life Inventory for Parents of Chronically Ill Children (ULQIE)	Quality of life of parents	29 Items	(63)
	Mindfulness Attention Awareness Scale (MAAS-5)	Parental mindfulness	5 Items	(53, 54)

**Table 2 tab2:** Diagram of trial activities and measurement time points.

	Study period								
	Enrollment			Intervention		Post-intervention and follow-up		Post-data collection	
Timepoint/Content	Screening (<4 weeks before baseline)	Baseline assessment (week 0)	Allocation	Res@t intervention (week 1–9 and week 15 [booster])	TAU	Post-intervention (week 10)	Follow-up (week 20)	Res@t intervention	TAU
*Enrollment*									
Eligibility screening	X								
Clinical assessment	X								
Informed consent	X								
Randomization IG/CG			X						
*Interventions*									
Intervention group (adolescent-parent dyads)				X	X				X
Waitlist control group (adolescent-parent dyads)					X			X	X
*Assessments*									
Adolescents						IG/CG	IG/CG		
Sociodemographics	X	X							
Media use	X								
GADIS-A	X					X	X		
SOMEDIS-A	X					X	X		
STREDIS-A	X					X	X		
SDQ	X					X	X		
PSQI		X				X	X		
ESS-CHAD		X				X	X		
PSS-10		X				X	X		
Family APGAR		X				X	X		
FCS		X				X	X		
MAAS-5		X				X	X		
Parents						IG/CG	IG/CG		
Sociodemographics		X							
Parental media use		X							
GADIS-P	X					X	X		
SOMEDIS-P	X					X	X		
STREDIS-P	X					X	X		
SDQ-f	X								
Media Rules		X				X	X		
Family APGAR		X				X	X		
FCS		X				X	X		
PHQ-9		X							
GAD-7		X							
EEI-R		X							
FSW		X				X	X		
PSS-10		X				X	X		
ULQIE		X				X	X		
MAAS-5		X				X	X		

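### Three named secondary outcomes (parent-rated SDQ, adolescent media-use time, parental media use) have no post-baseline assessment in Table 2, and the clinician rating is missing from the same schedule

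*Protocol article*

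**What the plan says.** Section 2.10.2 gives the adolescent secondary outcomes as including "adolescent emotional and behavioral problems (based on self-rating and parental rating), sleep-associated aspects, mindfulness, and psychological stress perception, media usage times". The parent list reads: "For the parents, these comprise mindfulness, quality of life, parental media usage, media rules, parental self-efficacy, and family communication/functioning". Section 2.12 says the secondary endpoints are explored with methods analogous to the primary analysis, which models change from baseline to post-treatment.

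Table 2, captioned "Diagram of trial activities and measurement time points", gives the timing of each instrument. Section 2.6 points to it as the questionnaire schedule and says the platform presents questionnaires automatically at the protocol time points, without the clinician. In Table 2, SDQ-f and adolescent *Media use* are marked at screening only, and *Parental media use* at baseline only.

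On the clinician rating, the third primary hypothesis in section 1.1 is that Res@t plus TAU "reduces symptoms of specific DMUD in adolescents assessed by their treating clinicians compared with TAU, measured as change from screening to post-intervention". Table 2 has one clinician-related row, *Clinical assessment*, marked at screening only. The abstract states: "All outcomes will be assessed using standardized self-report measures".

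**The concern.** A secondary outcome of a randomized comparison needs at least one value after baseline in both arms. Section 2.10.2 calls three measures outcomes, and the only schedule shown collects each of them once, before treatment. Because questionnaires are issued automatically, a missing mark carried into the platform configuration means the questionnaire is never sent. An analysis plan cannot repair that, since a week-10 or week-20 answer cannot be obtained once the visit has passed.

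Two of the three measures describe media-use behaviour in the family, which is what the intervention targets. The third is the parents' view of the adolescent's mental health. Section 4 itself warns that affected adolescents may understate their symptoms, which gives the parent report a value of its own.

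The clinician rating raises a related but weaker question: the schedule and the abstract do not reflect a measurement that a confirmatory hypothesis requires.

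**Working it through.** The check is a comparison of the outcome list with the schedule. The plan states no figure on this point that could be reproduced.

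**Step 1. Outcomes in section 2.10.2 against Table 2 (item counts from Table 1).**

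| Outcome | Instrument (items) | Screening | Baseline | Week 10 | Week 20 |
|---|---|---|---|---|---|
| Parent-rated emotional/behavioral problems | SDQ-f (25) | X | – | – | – |
| Adolescent media-use time | Media use (13) | X | – | – | – |
| Parental media use | Parental media use (6) | – | X | – | – |
| *Comparator:* self-rated SDQ | SDQ (25) | X | – | X | X |
| *Comparator:* media rules | Media Rules (6) | – | X | X | X |
| *Comparator:* parental self-efficacy | FSW (9) | – | X | X | X |

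The three rows in question have 0 of 2 post-baseline marks and the comparators have 2 of 2. Neighbouring rows keep their later marks, so the blanks are not a fault of text extraction.

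**Step 2. Could single measurement be intended?** PHQ-9, GAD-7 and EEI-R are also measured once. That is consistent, because section 2.10.3 names parental mental distress and parenting style as covariates. SDQ-f and parental media use are given no such role; section 2.10.2 calls them outcomes. Section 2.10.3 does mention media usage time again, beside the app-usage data, but gives no time point or instrument for it.

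**Step 3. Could another source fill the gap?** Section 2.9 describes a daily calendar that includes usage times, as part of the intervention. The same section releases the app to controls only once their own data collection is finished, and the Figure 1 footnote agrees. Before week 20 the calendar can therefore describe the intervention group only. It yields post-baseline usage times in one arm, not a comparison. It offers no substitute for SDQ-f, and no documented one for parental media use in the control group.

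**Step 4. The clinician rating.**
- For a post-intervention rating: section 1.1 (third hypothesis); section 2.6, which places clinical assessments at screening, baseline, week 10 and week 20 and mentions a post-treatment evaluation apart from the digital questionnaires; section 2.10.1, which describes the clinician checklist and has the primary outcome assessed at enrollment, post-intervention and follow-up.
- Not reflecting it: Table 2 ("Clinical assessment X", screening column only) and the abstract sentence on self-report.

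The rating is planned in the text and absent from the schedule.

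**Step 5. Burden of adding the marks.**
- Adolescents: 13 items more. The instruments now marked at week 10 total 10+10+10+25+24+8+10+5+10+5 = 117 items, so the increase is 13/117 = 11%.
- Parents: 25 + 6 = 31 items more. The instruments now marked total 10+10+10+6+5+10+9+10+29+5 = 104 items, so the increase is 31/104 = 30%.

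The same holds at week 20, where the same instruments are marked. These totals assume that every marked instrument is presented in full.

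**The case against.** A reader might infer from Table 2 that the third primary hypothesis has no scheduled endpoint. The documents do not support that. The text of sections 1.1, 2.6 and 2.10.1 plans a clinician rating after the intervention. The single *Clinical assessment* mark sits in the Enrollment block, beside eligibility screening and consent, and reads as an enrolment step. The Assessments block covers adolescent and parent questionnaires only, and section 2.6 describes the table as a questionnaire schedule. What stands is a mismatch: a table captioned as covering trial activities leaves out a confirmatory measurement that the text plans. The abstract sentence is condensed wording on which no procedure depends, but it does not fit a clinician-rated hypothesis.

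A reader might also say that no media-use data will exist after baseline in either arm. That goes too far, since the intervention group's calendar would produce some. Section 2.11 says all data are collected through the Res@t application, which could suggest some control-arm capture, but no control-arm measurement of usage time after baseline is named. The absence of a documented comparison stands.

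On weight, three counterpoints are fair. The secondary endpoints are exploratory under section 2.12. The self-rated SDQ, the other view of the same construct, is repeated at both later visits. And the full protocol and platform configuration are not shown, so the fault may lie in section 2.10.2 rather than in Table 2. These limit the severity, but the two statements still cannot both be right.

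**Conclusion.** The inconsistency is real. Three secondary outcomes named in section 2.10.2 have no post-baseline questionnaire in Table 2, so as scheduled neither a change score nor a between-arm comparison is possible from those instruments. The consequence is conditional on the platform following Table 2 as printed; if the operational schedule already repeats them, only the article needs correcting.

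The clinician-rating point is smaller: the measurement is planned in the text, and the table and abstract should be brought into line with it.

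The effect is confined to exploratory outcomes and reporting. The adolescent and parent scales for the first two primary hypotheses are marked at week 10 and week 20, and no confirmatory test, sample size or power figure changes. It is worth correcting while visits can still be scheduled, but it does not threaten the primary analysis.

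**What to change.** 1. Check the platform schedule against Table 2 and decide, for each of the three instruments, whether repetition is intended.
2. Where it is, add week-10 and week-20 marks in both arms for SDQ-f, adolescent media use and parental media use. The cost is a scheduling change, a short amendment, and 13 more adolescent and 31 more parent items per visit. The parent increase is the larger in relative terms and should be weighed against the 40% dropout assumed before week 10.
3. Where it is not, delete the item from section 2.10.2 and describe it as a baseline characteristic. This costs nothing in burden but gives up the outcome.
4. Add a clinician-rating row to Table 2 at screening, week 10 and week 20, as the text already plans, and reword the abstract sentence to cover adolescent, parent and clinician ratings. This is editorial only.

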#### Additional variables

2.10.3

Additional variables that will be included as covariates cover sociodemographic information (age, sex/gender, region of living, and parental status), parental mental distress, and parenting style (Table 1). Moreover, data on media usage and app usage patterns, i.e., media usage time as well as number of app usage sessions, days, weeks, quests started, quests completed, mindfulness exercises observed, and calendar entries, as well as the relative completion of modules and complete training will be collected.

### Data collection and management

2.11

All data will be collected on an ongoing basis via the Res@t application and stored within the ISO-certified Embloom platform on secure servers with regular backups. Data will be pseudonymized before transferring it in an encrypted form to the secure UKE server. Sensitive participant data will be accessible only to the treating practitioner within individual digital patient folders (within the recruitment center) and authorized admins of Embloom (across the recruitment centers). The latter will have the primary responsibility for verifying the integrity of the database and securing pseudonymized data transfer. A statistician at the UKE who is independent of the evaluation team will monitor trial conduct and data collection manually in addition to automatic monitoring of data completeness by the software. Moreover, pseudonymized data will be reprocessed to fit all structural requirements for the analyses. The principal study center at the DZSKJ will be responsible for managing and archiving the transferred database after analysis. All participant data will be always handled confidentially and in accordance with the General Data Protection Regulation (GDPR).

### Data analysis

2.12

Data will be analyzed by the independent statisticians at the IMBE with sophisticated experience in multicenter therapy studies. Descriptive statistics will be presented with respect to both the entire sample and group-wise. The primary analysis is based on the intention-to-treat (ITT) approach with all randomized patients. The significance level will be set at 5% (two-sided). All three primary hypotheses are structured hierarchically. The second primary hypothesis will only be evaluated in a confirmatory way if the first primary hypothesis leads to a significant test result. The third primary hypothesis will only be evaluated in a confirmatory way if the second primary hypothesis leads to a significant test result. For the analysis of each primary hypothesis, a linear mixed model with implicit maximum likelihood correction of missing values under the missing-at-random assumption will be calculated, respectively. The change in DMUD symptoms from baseline to post-treatment will be used as an outcome variable, randomization group, type of DMUD (social media, gaming, streaming), recruitment site size and location as fixed effects, individual recruitment site and patient nested within site as random effects, and the baseline DMUD score as a covariate. The interaction between the randomization group and media usage pattern (hazardous vs. pathological) as well as effects of incomplete dyads will be tested within secondary analyses.

To examine the impact of missing values on the outcome of the primary analysis, sensitivity analyses will be performed using multiple imputation methods to replace missing values. The primary endpoint at follow-up and the secondary endpoints will be investigated exploratorily using analogous methods, which are adequate for the scale type. The following subgroup analyses are planned: severity of DMUD, sex, education, and socioeconomic status. Qualitative assessments of treatment provider satisfaction will be supplemented. Details of the analysis will be specified in a statistical analysis plan. The analysis will be performed with the latest version of the software package R (70).

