### Sample size calculation

2.4

The sample size was computed with the procedure tests for Two Means in a Cluster-Randomized Design in PASS 16.0.4 (NCSS, LLC. Kaysville, Utah, United States). A small standardized mean difference (Cohen’s *d* = 0.2) between IG and CG in symptom reduction measured as change from baseline to post-intervention is assumed. The number of study centers is assumed to be 50, each recruiting 27 patients on average. This leads to a feasible sample size of 667 per group. The coefficient of variation of the cluster sizes is set to 0.4 because recruitment is assumed to be heterogeneous due to the different sizes of the study sites. The intra-cluster correlation (ICC) is set to 0.005. With the achievable sample size of 667 patients with respective parents in each of the two groups (*N*_dyads_ = 667) and a two-sided type I error of 5%, the power will be 77%. A dropout rate of 40% before post-intervention assessment (10 weeks) and 20% before follow-up (20 weeks) is assumed. The sample size calculation refers to the three primary hypotheses, taking into account the hierarchical structure. A drop-out rate of 40% before post-intervention assessment (week 10) is considered. With an estimated proportion of adolescents in the outpatient setting with hazardous or disordered digital media use of 20% and a participation rate of 50%, *N* = 13,340 patients must be initially screened. Due to the novelty of the study, conservative estimates were chosen for the assumed effect size and drop-out and participation rates. Digital CBT-based intervention studies with comparable adolescent age groups reported small to medium effect sizes regarding the reduction in depression and anxiety symptoms (36, 37).

Three nuisance parameters (drop-out rate, coefficient of variation, and intraclass correlation coefficient) enter the sample size planning, the assumptions of which are not known with certainty. Therefore, a blinded interim analysis will be performed after the collection of post-intervention data from half of the planned patients (200 per group, 400 total) to estimate the nuisance parameters and possibly adjust the sample size.

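### The primary model pairs one change score per patient with a patient random effect it cannot identify, and its stated missing-data correction is a complete-case analysis of about 800 of the 1,334 dyads

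*Protocol article*

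**What the plan says.** Section 2.12 (Data analysis) defines the response: "The change in DMUD symptoms from baseline to post-treatment will be used as an outcome variable". Section 2.10.1 (Primary outcome) agrees that a single difference is meant, although it counts from screening: "The differences between screening and post-intervention total scale scores will be investigated primarily". Each rater has its own model, and the method is described as follows: "a linear mixed model with implicit maximum likelihood correction of missing values under the missing-at-random assumption will be calculated". The fixed effects are group, DMUD type, site size and site location. The remaining terms are "individual recruitment site and patient nested within site as random effects, and the baseline DMUD score as a covariate". No time effect is listed.

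Week 20 lies outside the primary model: "The primary endpoint at follow-up and the secondary endpoints will be investigated exploratorily using analogous methods".

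Section 2.12 says the primary analysis follows intention-to-treat with every randomized patient, and the Abstract puts 1,334 dyads in the primary analyses. Section 2.4 (Sample size calculation) says: "A drop-out rate of 40% before post-intervention assessment (week 10) is considered". Imputation is kept for a secondary role: "sensitivity analyses will be performed using multiple imputation methods to replace missing values".

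**The concern.** Two features of this model belong to a longitudinal analysis: a patient-level random effect, and the property that likelihood makes use of partly observed patients. The response, however, is one change score. With a single response per patient, the random effect has nothing to separate from the residual. The likelihood also has no second response through which a patient missing week 10 could still contribute.

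At stake is the description of the confirmatory analysis. As written, a report could claim an analysis of all randomized patients with a built-in correction for missing data when neither holds and about two in five dyads are absent. The mismatch also leaves two different primary models open, change-score or repeated-measures, and that choice should not be made after data are seen.

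**Working it through.** **1. Reproduce the stated power.** Inputs from Section 2.4: d = 0.2, 667 per group, 50 sites, CV of cluster size 0.4, ICC 0.005, two-sided 5%, 40% dropout before week 10. I assume 25 sites per arm.

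Design effect DE = 1 + [(1 + CV²)·m − 1]·ICC; effective n = n/DE; power = Φ(d·√(n_eff/2) − 1.96).

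- Completers only: 667 × 0.6 = 400 per arm, m = 400/25 = 16. DE = 1 + (1.16 × 16 − 1) × 0.005 = 1.088; n_eff = 368; power = 77.4% (75.7% with t on 48 df).
- Everyone: 667 per arm, m = 26.68. DE = 1.150; n_eff = 580; power = 92.6% (91.6% with t).

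The stated 77% therefore assumes 400 completers per arm. Two other figures in Section 2.4 agree. The interim look calls 200 per group half of the planned patients. The screening number gives 13,340 × 0.20 × 0.50 = 1,334, so 1,334 is the number enrolled before dropout.

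**2. Count the responses per patient in one primary model.** Raters are in separate models. Week 20 is a separate exploratory analysis. The pre-treatment score is a covariate. Table 2 schedules the DMUD scales only at screening, week 10 and week 20. One response remains: the change to week 10.

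**3. Identifiability.** For patient j at site i, Var(y_ij) = σ²_site + σ²_patient + σ²_residual, and Cov(y_ij, y_ik) = σ²_site for two patients at the same site. The patient and residual variances enter only as a sum.

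- Simulated trial with 1,321 patients, 795 with a week-10 score, site variance 0.005, patient plus residual variance fixed at 0.995. Setting the patient part to 0, 0.25, 0.50, 0.75 and 0.95 gives the same log-likelihood (−1138.986), treatment estimate (−0.168) and SE (0.074) each time.
- In R, the software the protocol names, on 50 × 27 = 1,350 simulated patients (821 with a score): lme4 stops because there are as many patient levels as observations. nlme runs, but gives a patient variance of 1.017 against a residual of 0.0001, and cannot form intervals for the variance components. Its treatment estimate is −0.154 (SE 0.070) with or without the patient term.

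**4. What the likelihood does with a missing week-10 score.** A patient whose only response is missing contributes a factor of 1. In the R run, 821 of 1,350 patients were used. At the plan's 40%: 1,334 × 0.40 ≈ 534 dyads contribute nothing and about 800 are analysed.

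**5. Would adding week 20 recover them?** I compared complete-case ANCOVA with joint maximum likelihood over weeks 10 and 20 in 400 simulated trials of 1,334 patients, with an assumed week-10/week-20 correlation of 0.6.

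| Dropout pattern | SD of estimate, complete case | SD, joint model |
|---|---|---|
| Monotone | 0.0632 | 0.0632 (estimates correlate 1.000) |
| 30% of week-10 non-responders return at week 20 (assumed) | 0.0636 | 0.0617 |

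The gain comes only from patients who miss week 10 and return.

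**The case against.** The best defence is that the patient term is harmless: an analyst would meet the error, drop the term and get the same estimate and SE. That stands. A reader might infer that the trial cannot be analysed, and the fits above do not support this. The term may also be a trace of a repeated-measures model shortened for the article, to be set out in the SAP. That is possible, but the article does not just omit detail. It fixes the response, covariate and random effects and claims a property that this combination lacks.

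Second, complete-case ANCOVA is legitimate under missing-at-random if dropout depends only on what is modelled: group, DMUD type, site size, location, site and baseline score. This also stands. The fault lies in the claimed correction and analysis set, not in an estimate known to be wrong.

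Third, a reader might infer that the sample size fails or that a specific bias is built in. Neither follows. The loss is already in the 77%. As for bias, a scenario can be constructed with no true effect, random dropout in controls, 40% dropout in the intervention arm driven by the parent's week-10 rating, and an adolescent–parent correlation of 0.5. It gives a false benefit of 0.036, 0.065 and 0.132 SD for log-odds slopes of 0.25, 0.5 and 1.0, which is 18%, 33% and 66% of d = 0.2. A simpler scaling gives 0.05, 0.10 and 0.17 residual SD. Every driver of these figures, including the sign, is assumed; the protocol says only that agreement between the two raters was moderate.

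Fourth, imputation is already planned, and incomplete dyads will be analysed. The content of the imputation model and any analysis departing from missing-at-random can properly be left to the SAP, so their absence is not criticised here.

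**Conclusion.** Wrong as written, and inexpensive to repair. The patient-within-site variance is not identifiable with one change score per patient, although this leaves the treatment effect and its SE unchanged. The weightier part is that the implicit maximum likelihood correction is a complete-case ANCOVA with a site effect. At the plan's 40% dropout it uses about 800 of 1,334 dyads, so the statements in Section 2.12 and the Abstract about who enters the primary analysis are not met. Power of about 77% stands, assuming 25 sites per arm. Validity rests on week-10 dropout depending solely on the modelled covariates. Departures from that could bias the contrast, but their size and direction cannot be derived from the document.

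**What to change.** In Section 2.12 and the SAP, delete the patient random effect, keep the site random intercept, and state that the likelihood analysis uses patients with a week-10 score. Correct the Abstract to match.

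If the all-randomized claim is to be kept, promote the multiple imputation already planned to the primary missing-data handling. Carry it out by arm, respect site, and use post-baseline scores already collected: the other raters' week-10 ratings, week-20 scores and the adolescent SDQ.

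Alternatively, model the week-10 and week-20 scores as repeated measures with group-by-visit, the pre-treatment score as covariate, and site and patient effects, with the week-10 contrast as the primary test. The patient effect is then identifiable. State that this recovers information only from patients who miss week 10 but return at week 20.

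The cost is wording and a little programming, with no new data or patients. The limit is that imputation helps only where another score exists from the dyad or clinician. In a simplified version of the scenario under the objection (slope 0.5, correlation 0.5), the bias left after imputing from the parent score was 0.002 if every parent stayed, 0.035 if half left with the adolescent, 0.065 if 80% left, and 0.099 if all left. The last figure is no better than complete case.
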